## Results

4

Figure 4 shows a flowchart of the participant enrolment and completion of the RepEAT study. In total, 506 individuals showed interest in the study, of whom 223 were still interested and scheduled for an information session after receiving the written participant information. After having received the written and verbal information, 133 individuals signed the informed consent form and underwent the screening procedure. Of these 133 individuals, 63 individuals were eligible according to all inclusion and exclusion criteria, and were included in the study. During the study, 10 participants dropped out (15.9% drop-out rate) at different stages of the study and for different reasons (depicted in Figure 4). 53 participants completed the study, which is well within the beforehand estimated sample size range of 44–82 participants.

**Figure 4 fig4:**
[figure not shown]
Flowchart of enrolment and completion of study participants.

The baseline characteristics of all participants that started the dietary intervention (*n* = 60) are depicted in Table 2. Participants were on average 63.9 (± 8.3) years old with a BMI of 30.3 (± 4.0) kg/m^2^, and 45% of the study population were women. In total, each participant who completed the study consumed 378 meals and we collected ~6,000 interstitial glucose concentrations per individual over the 9-week dietary intervention.

**Table 2 tab2:** Baseline characteristics of participants who started the dietary intervention (*n* = 60).

Age (years)	63.9 ± 8.3
Women (*n*, %)	27 (45%)
Weight (kg)	90.6 ± 14.3
BMI (kg/m^2^)	30.3 ± 4.0
Waist circumference (cm)	106.0 ± 12.2
Waist-to-hip ratio	1.0 ± 0.1
SBP (mmHg)	128.9 ± 18.9
DBP (mmHg)	74.2 ± 10.8
Use of antihypertensives (*n*, %)	11 (18%)

Categorical data are depicted as *n* (%), numerical data are depicted as mean ± SD. BMI, body mass index; DBP, diastolic blood pressure; SBP, systolic blood pressure.

## Discussion

5

This manuscript describes the protocol of the RepEAT study, which was designed to answer the question: “how replicable are glucose responses within individuals and how consistent is the variation in glucose responses between individuals under standardized conditions of a 9-week fully controlled dietary intervention?”. Furthermore, we aim to examine how this person-specific variation in glucose responses to meals is related to the diet, the time of consumption, and to an individual’s phenotype. To measure glucose responses in a standardized setting, the RepEAT study was a fully controlled dietary intervention study of nine weeks, including three repetitions of a 3-week menu cycle. Before the start of the dietary intervention, participants were comprehensively characterized to study associations between postprandial glucose responses and phenotype.

Up to now, most evidence regarding postprandial glucose responses and variation between and within individuals originates from cohort studies, with only a few standardized meals next to the habitual diet of participants (4, 6, 8). By making use of a fully controlled dietary intervention with continuous glucose and physical activity monitoring, the RepEAT study will provide further insight in the variation in glucose responses independent of external factors such as physical activity, previous meals, and time of day. Moreover, the degree of insulin resistance is an important factor affecting postprandial glucose responses. In the RepEAT study, insulin resistance is determined by an oral glucose tolerance test and will be used to correct for an individual’s insulin resistance status. In addition, all meals were consumed according to a schedule with at least two hours in between meals and snacks to enable us to determine the full glucose response, since on average the glucose concentration returns to baseline within two hours. Furthermore, in order to examine the variation in glucose responses to identical meals and food products within an individual, the 9-week diet consisted of three identical periods of three weeks, resulting in three repetitive measures of postprandial glucose responses to all meals and food products. Given the standardized dietary background, these three repetitive measures per meal and food products will be analysed to measure the robustness of postprandial glucose responses within an individual. Within each three-week period, different versions of the same food product and meal were consumed at the same weekday and time of day, which enables us to study glucose responses to variations of the same food product or meal.

In conclusion, with the RepEAT study we will provide an answer to the question whether person-specific glucose responses to meals are unique and robust enough to be able to be used in personalized advice.

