## Abstract

**Introduction:**

An elevated postprandial glucose response is associated with an increased risk of cardiometabolic diseases. Existing research suggests large heterogeneity in the postprandial glucose responses to identical meals and food products between individuals, but the effect of other consumed meals during the day and the order of meals during the day on the heterogeneity in postprandial glucose responses still needs to be investigated. In addition, the robustness of the glucose responses to meals or foods is still unknown.

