**Objectives:**

The overall aim of the project is to assess whether the glucose response to a meal is sufficiently person-specific to use in personalized dietary advice. We aim to answer the question: “How replicable are glucose responses to meals within individuals and how consistent is the variation in glucose responses between individuals?”

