**Methods:**

The question will be assessed under standardized conditions of a 9-week fully controlled dietary intervention in which all meals are the same between individuals and consumed in a fixed order at a fixed time. 63 apparently healthy men and women with a BMI of 25–40 kg/m^2^ and aged 45–75 years were enrolled in the RepEAT study (NCT05456815), of whom 53 participants completed the study. The RepEAT study comprised a fully controlled dietary intervention of nine weeks, consisting of three repetitive periods of three weeks. Within each three-week period, a variety of meals and food products were offered during breakfast, lunch, dinner and in between meal snacks. Throughout the dietary intervention, glucose was continuously monitored using Freestyle Libre Pro IQ monitors. Physical activity was monitored using the ActiGraph and ActivPAL. To measure the association between glucose responses and an individual’s phenotype, various measurements were performed before the start of the dietary intervention including an oral glucose tolerance test, a high-fat mixed meal challenge, assessment of body fat distribution including liver fat (MRI/MRS), and cardiometabolic markers.

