### Study design

2.1

The RepEAT study was a fully controlled dietary intervention trial carried out at Wageningen University & Research (WUR), Netherlands. The study was conducted between August and December 2023, and the project is currently in the phase of data cleaning. The study was approved by the Medical Ethics Committee Oost-Nederland, Netherlands (NL80179.091.21) and was registered at ClinicalTrials.gov (NCT05456815). The RepEAT study was conducted according to the Declaration of Helsinki (15), and all participants signed a written informed consent prior to the start of the study.

This fully controlled dietary trial consisted of a 9-week dietary intervention (Figure 1). The primary outcome of the study is the person-specific glucose responses as measured by the 2 h incremental area under the curve (iAUC). Glucose responses will be measured using continuous glucose monitoring. Glucose was continuously monitored throughout the 9-week dietary intervention to determine glucose responses to all food products and meals during the intervention. To prevent an effect of preparation of meals on the glucose response, all meals and food products were prepared and provided by the research facility. To enable the assessment of postprandial glucose responses to all meals and food products without interference of other meals, all meals and food products were consumed according to a fixed schedule with at least a two-hour interval between all meals and snacks. Physical activity was continuously monitored throughout the dietary intervention to assess physical activity patterns. To determine potential associations between an individual’s phenotype and their postprandial glucose response, participants were comprehensively characterized before the start of the dietary intervention. To assess whether consumption of a controlled diet for nine weeks reduced the overall variation in these characteristics, some of the baseline measures were repeated at the end of the dietary intervention (Figure 1).

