#### OGTT and HFMM

2.2.2

To characterize the metabolic response to a meal challenge and to determine insulin resistance, a 7-point oral glucose tolerance test (OGTT) and a high-fat mixed meal (HFMM) test were performed once per individual in the characterization period. The evening before both the OGTT and the HFMM, participants consumed a standardized dinner (24% of energy intake (en%) fat, 54 en% carbohydrates, 22 en% protein; in total 2,380 kJ/565 kcal). After the standardized dinner participants remained fasted until arriving at the research facility. In addition, participants refrained from heavy exercise the evening before and the morning of these tests. Thirty minutes before the start of the test, a venous catheter was placed.

For the OGTT, at *t* = 0 min, participants drank 200 mL of a 75 g glucose solution (Glucomedics, Breda, The Netherlands) within five minutes. Blood was collected in the fasted state before (*t* = 0), and 15, 30, 45, 60, 90, and 120 min after consumption of the glucose solution, to measure plasma glucose and insulin concentrations. The HFMM was provided in the form of a shake and consisted of 320 g water, 20 g protifar, 83.5 g dextrose, 60 g palm olein, and 20 drops of vanilla oil. In total, the shake contained 3,833 kJ and 76.3 g carbohydrates, 17.6 g protein, and 60 g fat (24). To make sure there was no difference in metabolic response due to a difference in consumption speed, participants were instructed to consume the drink in 10 min. Blood samples were collected before consumption (*t* = 0) and 30, 60, 90, 120, 180, and 240 min after the consumption of the HFMM for the measurement of plasma glucose and insulin, free fatty acids, short-chain fatty acids, triglycerides, cholesterol, gut hormones, metabolomics, and proteomics including cytokines. At each time point, the first 2 mL of blood was discarded before drawing the blood samples because it could still contain the physiological salt of the venflon line.

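### The claim that two-hour spacing frees responses from previous meals rests on an average, and three repeats of one fixed sequence cannot separate a person's response to a later meal from that person's residual glucose after the meal before it

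*Protocol article*

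**What the plan says.** - **Spacing and its purpose.** Section 2.1 of the protocol article states that "all meals and food products were consumed according to a fixed schedule with at least a two-hour interval between all meals and snacks". The aim given there is "To enable the assessment of postprandial glucose responses to all meals and food products without interference of other meals".
- **Justification.** The Discussion says that the gap allows the full response to be determined, "since on average the glucose concentration returns to baseline within two hours". It also promises insight into variation that does not depend on previous meals, among other external factors. No other support for the two-hour figure is given.
- **Level of the aim.** The Abstract asks whether the response to a meal is "sufficiently person-specific to use in personalized dietary advice".
- **Order.** The Abstract says that "all meals are the same between individuals and consumed in a fixed order at a fixed time". The Discussion describes the three 3-week periods as identical, and section 2.1.3 says the reference and reformulated products were repeated as an exact copy in periods two and three.
- **Analysis.** Section 3 judges replicability by comparing the three repetitions and runs the iAUC from the last reading before eating to 120 min. It corrects for insulin sensitivity through the person's average response and/or the OGTT, and for physical activity. Section 2.4 reads a low correlation between a food's response and the person's average as a sign of a person-specific response.

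**The concern.** An average return to baseline within two hours is compatible with some participants returning later. For such a person the next meal starts on a falling curve, and its iAUC is shifted by an amount that depends on what was eaten before. If the predecessor stays the same, the shift recurs in each cycle. It then looks like a replicable feature of that person's response to the second food.

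The plan's own criteria could accept this as a positive finding. A shift tied to one predecessor can pull a food's response away from the person's average, which section 2.4 reads as person-specific, and it also replicates, which section 3 reads as robust. Advice about a food could then rest on a slow return after a different food. Holding the predecessor constant standardises its effect but does not make the result independent of it.

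**Working it through.** The plan gives no figure for carry-over, so there is none to reproduce. Four steps show what the stated design can and cannot identify.

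**1. How many occasions are exposed.** Section 4 reports 378 meals per completer over nine weeks. 378 / 63 days = 6 occasions a day, so on average about five of six follow another occasion on the same day. The actual gaps are not shown; two hours is the minimum.

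**2. Direction and size of the shift in one iAUC.** Assume a residue of h mg/dl above fasting level at meal start, decaying exponentially with time constant tau (hours). With the last pre-meal reading as baseline (section 3), the change in the 2 h net area is

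−h × [2 − tau × (1 − exp(−2/tau))].

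At tau = 1 h the bracket is 2 − (1 − 0.135) = 1.135, which gives:

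| h (mg/dl) | Change in iAUC (mg/dl*h) |
|---|---|
| 10 | −11.4 |
| 18 | −20.4 |
| 25 | −28.4 |

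Over tau from 0.75 to 1.5 h the extremes are 10 × 0.895 = 9.0 and 25 × 1.302 = 32.6. Baseline subtraction therefore does not remove the residue; it turns it into a downward shift, so a slow returner can look like a replicable low responder to the next meal. Measured from fasting level instead, the same residue would add area: 10 × (1 − 0.135) = +8.6 at tau = 1 h. These are net areas. If only area above baseline is counted, the loss is smaller by an amount that depends on the shape of the curve.

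**3. What the stated correction removes.** Write the shift for person i at meal m as a part common to all of that person's meals plus a part specific to the predecessor of m. Adjusting for the average response or the OGTT can absorb the first part. It cannot absorb the second, and under a fixed sequence the second part is present in all three repeats.

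**4. Does this produce replicability from nothing?** A simulation used 53 people, 21 days of 6 occasions and 3 repeats, with no true person-by-meal effect. Assumed values were a residual SD of 20 and a between-person SD of 15 mg/dl*h, with slow return in half the people. The response was taken as the deviation from the person's own average. The table gives the mean ICC over the three repeats for occasions other than breakfast.

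| Carry-over SD (mg/dl*h) | Fixed predecessors | Predecessors permuted between cycles |
|---|---|---|
| 0 | 0.00 | 0.00 |
| 5 | 0.01 | −0.01 |
| 10 | 0.04 | −0.02 |
| 20 | 0.14 | −0.03 |

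The largest single-occasion ICC under the fixed order rose from 0.21 to 0.27, 0.46 and 0.75. The value of 0.21 at zero carry-over is pure selection of a maximum, so only the increase is informative. Breakfast, which has no same-day predecessor, also picked up an artefact (ICC 0.40 at carry-over SD 20), because the average subtracted from it contained the carry-over of the other meals.

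**The case against.** The strongest reply is that the fixed order is deliberate. The Introduction names the second-meal effect and time since the previous meal, and argues that standardising both is essential. The research question is put under standardised conditions, and varying predecessors would bring back the variation the design removes. That stands: the fixed order is a defensible choice and is not criticised here. What does not follow from it is independence from previous meals.

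A second reply is that a pre-meal glucose term belongs in an analysis plan that is not shown. Its absence alone would indeed be no finding. The finding is that the article claims more than the stated design and criteria can deliver.

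A third is that predecessors are not perfectly constant. Point-system foods are self-chosen (5%–10% of the diet), participants could switch energy group, and two Saturdays shifted the eating window. First-of-day meals have no same-day predecessor. This is correct, and carry-over would not repeat identically. None of these is described as re-ordering the test items, however.

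Two stronger readings are tempting and unsupported. A reader might infer that the trial sets out to study meal order, because the Abstract says that "the order of meals during the day on the heterogeneity in postprandial glucose responses still needs to be investigated". That sentence is background on the field, and no stated objective includes meal order. A reader might also take the mixed-meal sampling at "30, 60, 90, 120, 180, and 240 min after the consumption of the HFMM" as evidence that glucose stays raised beyond two hours. That schedule also serves lipids, gut hormones and other analytes, and it says nothing about slow glucose return.

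**Conclusion.** The concern holds as a problem of identifiability and of over-claiming. The article supports a person-level claim with an average. Under its fixed sequence, three repeats cannot separate a person's response to a non-first meal from a residue specific to the preceding meal, and the average/OGTT correction leaves that part in place.

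The size in this trial is unknown. The documents give no residue, no rate of return and no share of slow returners. The shift of about 9 to 33 mg/dl*h for residues of 10 to 25 mg/dl is conditional on an assumed exponential decay and a net-area iAUC. In the simulation the average artefact is small (0.01 to 0.04) at modest carry-over and reaches 0.14 only when carry-over SD equals the assumed residual SD. It would therefore be wrong to conclude that the trial's replicability results are mainly carry-over. The supported conclusion is that the stated analysis cannot tell, although data already collected can go a long way towards showing it.

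**What to change.** In section 3, using the existing sensor traces:

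1. For each test meal, derive the pre-meal elevation above that morning's fasting level and the slope just before eating.
2. Report the observed share of occasions back at baseline at two hours, in place of the statement about the average.
3. Repeat the replicability and person-specific analyses as a sensitivity analysis with these two terms, and again on occasions that start at or near fasting level, within a margin set in advance. Show first-of-day meals separately. In the restricted analyses compute each person's average from the same restricted occasions, so that carry-over does not re-enter through the average.
4. Reword section 2.1 and the Discussion so that the conclusion is replicability within this fixed meal sequence, not independence from previous meals.
5. Reconcile the iAUC starting point: section 2.1.4 says the earliest time point before the meal, section 3 the latest. The baseline chosen affects the size, and can affect the sign, of any carry-over.

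The cost is two derived variables, one sensitivity model and one restricted analysis, with no new data. The article describes the project as in data cleaning, so these can still be specified before analysis. The price is fewer occasions in the restricted set, hence less precise estimates there, and a narrower conclusion.

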## Ethics statement

The studies involving humans were approved by Medical Ethics Committee Oost-Nederland, Netherlands. The studies were conducted in accordance with the local legislation and institutional requirements. The participants provided their written informed consent to participate in this study.
